### Data analysis

Data will be analyzed using IBM SPSS Statistics version 29.0 (IBM Corp., Armonk, NY, USA). Baseline characteristics will be summarized using descriptive statistics, including mean and standard deviation for continuous variables and frequencies and percentages for categorical variables. The primary analysis will follow the intention-to-treat (ITT) principle, whereby all randomized participants will be analyzed according to their originally allocated groups regardless of intervention adherence or withdrawal where possible. The ITT approach was selected to preserve the benefits of randomization, minimize attrition-related bias, and provide a pragmatic estimate of intervention effectiveness within a real-world school-based setting.

Missing data patterns will be examined, and the extent and reasons for missing data will be reported. Missing outcome data will be handled using appropriate imputation procedures, where necessary, to facilitate the inclusion of all randomized participants in the primary analysis, consistent with recommended approaches for randomized controlled trial analysis [23].

A mixed-design repeated-measures ANOVA will be used to examine group (intervention vs control) × time (baseline, mid-intervention [Week 4], and post-intervention [Week 8]) interaction effects for primary and secondary outcomes. Assumptions of normality, homogeneity of variance, and sphericity will be assessed using appropriate diagnostic procedures. Where the assumption of sphericity is violated, Greenhouse–Geisser correction will be applied. Significant interaction effects will be explored using post hoc pairwise comparisons with adjustment for multiple comparisons. Effect sizes for repeated-measures ANOVA will be reported using partial eta squared (η²p), while Cohen’s d will be calculated for post hoc pairwise comparisons, consistent with commonly recommended effect size reporting practices for intervention studies [12]. Statistical significance will be set at p < 0.05.

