### Sample size calculation

Sample size was calculated using G*Power version 3.1 for a mixed-design repeated-measures ANOVA examining the group × time interaction. Peak expiratory flow rate (PEFR) was selected as the primary outcome for sample size estimation. The selection of the effect size was informed by a previous randomized controlled trial investigating the effect of McKenzie exercises on pulmonary function among individuals with forward head posture, which demonstrated significant improvements in PEFR following the intervention [12]. To avoid overestimating the intervention effect and to ensure a conservative estimate for the present school-based posture education programme, a medium effect size (f = 0.25), alpha level of 0.05, and statistical power of 0.80 were used for the sample size calculation. The analysis indicated that a minimum of 28 participants per group was required. Allowing for an anticipated attrition rate of 20%, the target sample size was increased to 35 participants per group, resulting in a total planned sample of 70 students.

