### Outcome measures

Standardized outcome assessments will be conducted at baseline (Week 0), mid-intervention (Week 4), and post-intervention (Week 8). All assessments will be performed at approximately the same time of day to minimize physiological variability.

Primary outcome measures include lung function, postural alignment, and functional aerobic capacity. Postural alignment will be assessed using standardized posture grid analysis based on validated observational criteria [9,10]. Participants will stand in a standardized anatomical position in front of a calibrated posture grid, and alignment will be evaluated relative to vertical and horizontal reference lines to identify deviations in head position, shoulder symmetry, and spinal curvature. Posture grid assessment has demonstrated acceptable inter-rater and intra-rater reliability in previous adolescent posture assessment studies [9,10]. Standardized assessor training and assessment procedures will be implemented to support consistency during data collection.

Functional aerobic capacity will be assessed using the six-minute walk test (6MWT) conducted according to established guidelines [14]. Participants will be instructed to walk as far as possible along a standardized corridor for six minutes with consistent verbal encouragement. The total distance covered in meters will be recorded as the outcome measure. In addition to walking distance, participants’ heart rate, blood pressure, and oxygen saturation (SpO₂) will be measured before, during, and after the test. Perceived exertion will be assessed using Borg’s Rating of Perceived Exertion (RPE) scale, a validated tool used to measure subjective exercise intensity during physical activity [15]. The 6MWT has demonstrated good reliability and validity for assessing submaximal exercise capacity in adolescent populations [8,16]. Changes in walking distance will be interpreted alongside baseline performance and age-appropriate normative reference values derived from healthy children and adolescents [17].

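### The named repeated-measures ANOVA uses only students with all three visits, so with 20% attrition allowed for, the intention-to-treat aim rests wholly on an unnamed imputation

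*Protocol article*

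**What the plan says.** All references are to the Protocol article.

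- **Analysis set (Data analysis).** "all randomized participants will be analyzed according to their originally allocated groups regardless of intervention adherence or withdrawal where possible". The section justifies this partly as protection against bias from attrition.
- **Missing data (Data analysis).** Patterns, extent and reasons will be reported, and "Missing outcome data will be handled using appropriate imputation procedures, where necessary, to facilitate the inclusion of all randomized participants in the primary analysis". The type of imputation, the variables in it and the pooling rule are not given.
- **Model (Data analysis).** "A mixed-design repeated-measures ANOVA will be used to examine group (intervention vs control) × time", for primary and secondary outcomes, with Greenhouse–Geisser correction where needed and partial eta squared as the effect size.
- **Visits (Outcome measures).** "baseline (Week 0), mid-intervention (Week 4), and post-intervention (Week 8").
- **Attrition (Sample size calculation).** The calculation arrives at 28 students in each arm before losses, and the article then inflates this figure: "Allowing for an anticipated attrition rate of 20%, the target sample size was increased to 35 participants per group".

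**The concern.** A classical mixed-design ANOVA works on complete rows. A student absent at Week 4 is left out even if Week 8 was measured, and the reverse. The model that the plan fixes therefore cannot include all randomised students by itself, and it discards data already collected. Inclusion depends on an imputation step that the text does not name and makes conditional, while intention-to-treat is itself kept only as far as possible.

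Two procedures that fit this wording would cause trouble. A complete-case ANOVA is biased if students leave according to how they responded early on. A single fill-in treats invented values as observed, so standard errors are too small. The choice could also be made after the data have been seen.

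**Working it through.** **1. The plan's own figures.** Attrition step: 28 / (1 − 0.20) = 35 per group, 70 in total, which reproduces. Expected completers: 70 × 0.80 = 56 = 2 × 28, the stated minimum. If instead 10% were missing independently at each follow-up, 0.9 × 0.9 = 0.81 would be complete, a 19% loss and still within the allowance. So dropping incomplete students does not undercut the stated power target.

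The base figure of 28 per group depends on a correlation and a sphericity value that the article does not give. With f = 0.25, alpha 0.05, power 0.80, three visits and sphericity 1, the total needed is 54 at correlation 0 and 28 at correlation 0.5. That is a separate matter and does not affect this point.

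**2. Bias of a complete-case analysis.** The documents give no dropout mechanism, so all inputs here are assumptions: SD 1 at each visit, equal correlation ρ between visits, arm effects of 0, 0.25 and 0.50 SD at Weeks 0, 4 and 8, and 20% lost after Week 4. Control dropout is random. Intervention dropout depends on change from baseline to Week 4.

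- SD of the Week 4 change: s = √(2(1 − ρ)).
- Covariance of the Week 4 and Week 8 changes: 1 − ρ. The regression slope is (1 − ρ) / (2(1 − ρ)) = 0.5.
- *Extreme selection* (the poorest 20% of Week 4 changes leave): the retained mean shifts by 0.280 / 0.80 = 0.35 s, where 0.280 is the normal density at the 20th percentile.
- Completer estimate = 0.50 + 0.5 × 0.35 × s.

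| ρ | s | Completers, extreme selection | Completers, mild (logistic) selection |
|---|---|---|---|
| 0.5 | 1.00 | 0.50 + 0.175 ≈ 0.68 | 0.59 |
| 0.7 | 0.77 | 0.50 + 0.136 ≈ 0.64 | 0.57 |
| 0.8 | 0.63 | 0.50 + 0.111 ≈ 0.61 | 0.56 |

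The extreme column is 22–35% too large. The mild column uses a logistic dropout probability with slope about 1 per SD of Week 4 change. An analysis valid under missing at random (MAR) returns 0.50 in these settings.

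**3. Cases without bias, and a harsher one.** With dropout completely at random, complete cases are unbiased, at a small cost in precision (35 per group, adjacent-visit correlation 0.7: standard error 0.27, against 0.26 for likelihood-based analysis and for multiple imputation). If dropout depends on the Week 4 level and correlations are equal, the covariance of that level with the Week 8 change is ρ − ρ = 0, and simulation confirms a bias of about 0.00. If dropout depends on early change in opposite directions in the two arms, simulation gave 0.77 for complete cases, and 0.50 for both likelihood-based analysis and multiple imputation.

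**4. Single fill-in.** Carrying Week 4 forward in the extreme scenario gives 0.8 × (completer mean) + 0.2 × (0.25 − 1.40 s). At ρ = 0.5 this is 0.54 − 0.23 = 0.31; at ρ = 0.8 it is about 0.36. Single regression imputation within arm (35 per group, 20% missing at Week 8 at random, no true effect, equal correlations) raises the type I error of the interaction test from 5% to between 8% and 9%. Filling in the arm mean raises it to between 7% and 8%.

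**The case against.** The section does plan imputation, expressly so that all randomised students enter the primary analysis. Once values are filled in, the ANOVA drops nobody. A reader might infer that the plan contradicts itself, or that the stated method cannot deliver intention-to-treat. The text does not support that: the conditional wording can fairly be read as imputing wherever a value is missing, and single imputation is nowhere planned.

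A reader might also infer that a mixed model is the only remedy. It is not. Proper multiple imputation is valid under the same MAR assumption and performed equally well in the illustrations.

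The imputation model and pooling rule are commonly left to an analysis plan, which is not shown, so their absence alone is no fault. The bias figures describe an analysis that the wording permits but does not announce, under dropout that is assumed. The pilot reported satisfactory attendance and successful completion of assessments.

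All of this stands and limits the point. What remains is the choice the article does fix: a model that cannot use incomplete records, in a trial that allows for 20% attrition and cites attrition bias as a reason for intention-to-treat. Naming an imputation elsewhere would make that model workable. It would still leave the interaction F test, the Greenhouse–Geisser correction and partial eta squared to be pooled across imputed data sets, which the usual rules for estimates and variances do not cover directly.

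**Conclusion.** The point holds as a recommended improvement to the analysis choice. It is not an outright contradiction. The intention-to-treat aim depends entirely on an unnamed, conditional imputation because the named model needs all three visits.

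If the latitude were used for a complete-case analysis, a true 0.50 SD would be estimated as about 0.56–0.59 with mild and up to 0.68 with extreme selection on early change in the intervention arm. The estimate would be higher still if the arms selected in opposite directions, and there would be no bias if dropout is random. If the latitude were used for a single fill-in, uncertainty would be understated. These sizes rest on the assumed correlations and dropout mechanisms and are not forecasts for this trial. Neither the stated sample size nor the stated power target is affected.

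**What to change.** Before outcome data are examined by arm:

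1. For continuous outcomes, replace the repeated-measures ANOVA as primary analysis by a linear mixed model for repeated measures: SPSS MIXED, REML, arm, visit and arm-by-visit effects, unstructured covariance over the three visits, and Satterthwaite or Kenward–Roger degrees of freedom. Include every observed visit of every randomised student.
2. Name the Week 8 arm contrast (the difference between arms in change from baseline) as the main estimate, with its confidence interval.
3. Alternatively, keep the ANOVA framework with multiple imputation, stating the imputation model, its variables, the number of imputations and the pooling rule.
4. Remove the qualifiers that make intention-to-treat and imputation conditional, and rule out complete-case analysis and single fill-in as the primary analysis.
5. Add one delta-adjusted sensitivity analysis for departures from MAR.

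The cost is a change of wording and a different procedure in the software already planned, with no new data and no change in sample size. Reporting becomes slightly more complex. Partial eta squared is no longer the natural effect size, and a mean difference with a standardised version would take its place.

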Lung function will be evaluated using peak expiratory flow rate (PEFR) measured with a calibrated peak flow meter [18,4]. Participants will perform three maximal expiratory efforts from a standing position following standardized instructions, and the highest recorded value (L/min) will be used for analysis. PEFR is a widely accepted indicator of ventilatory capacity and pulmonary function in adolescent respiratory assessment. PEFR values will be interpreted with consideration of participant age, sex, and anthropometric characteristics where appropriate. Because PEFR is effort-dependent, standardized instructions, demonstration procedures, and repeated trials will be used to improve measurement consistency. PEFR values will be interpreted using age- and sex-appropriate normative reference values where available [18,4]. Although universally established MCID values for PEFR in healthy adolescent populations remain limited, changes in PEFR will be interpreted alongside baseline performance and repeated assessment trends. PEFR measurement has demonstrated acceptable validity and test–retest reliability in adolescent respiratory assessment when standardized instructions and repeated trials are applied [18,4].

Secondary outcome measures include resting cardiovascular parameters, physical activity level, psychological well-being, and ergonomic knowledge and behaviour. Resting blood pressure and heart rate will be measured using a validated automatic digital monitor following standardized procedures [5]. Physical activity level will be assessed using the International Physical Activity Questionnaire Short Form (IPAQ-SF), which evaluates time spent in walking, moderate-intensity activity, vigorous-intensity activity, and sedentary behaviour over the previous seven days [19]. It has been shown to be valid and reliable across multiple populations [19]. Psychological well-being will be assessed using the General Health Questionnaire-28 (GHQ-28), a self-report screening instrument comprising four domains, including somatic symptoms, anxiety and insomnia, social dysfunction, and depression [20]. The GHQ-28 has demonstrated good reliability and validity across different populations [20]. Knowledge, attitude, and practice related to ergonomic behaviour will be evaluated using a validated adolescent-adapted questionnaire assessing posture awareness, ergonomic practices, and behavioural habits in educational settings [21,22].

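### The omnibus group × time test with baseline as an outcome level is valid, but it is inefficient and unfocused for the Week 8 effect; a baseline-adjusted Week 8 comparison would serve better

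*Protocol article*

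**What the plan says.** The Outcome measures section sets three visits: "Standardized outcome assessments will be conducted at baseline (Week 0), mid-intervention (Week 4), and post-intervention (Week 8"). None is called the primary time point, but Week 8 is the only one described as post-intervention, and the programme lasts eight weeks.

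The Data analysis section applies one model to primary and secondary outcomes: "A mixed-design repeated-measures ANOVA will be used to examine group (intervention vs control) × time (baseline, mid-intervention [Week 4], and post-intervention [Week 8"). Two further sentences complete it: "Where the assumption of sphericity is violated, Greenhouse–Geisser correction will be applied", and "Significant interaction effects will be explored using post hoc pairwise comparisons with adjustment for multiple comparisons". The threshold is "Statistical significance will be set at p < 0.05". Effect sizes are partial eta squared for the ANOVA and Cohen's d for the pairwise comparisons. No baseline covariate appears.

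The sample size rests on the same test: "Sample size was calculated using G*Power version 3.1 for a mixed-design repeated-measures ANOVA examining the group × time interaction", with "a medium effect size (f = 0.25), alpha level of 0.05, and statistical power of 0.80 were used for the sample size calculation". It arrives at 28 per group, raised to 35 for 20% attrition.

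**The concern.** Two features of the named test do not suit the question of what an eight-week programme achieves.

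1. **Baseline enters as an outcome.** Chance differences between arms at Week 0 go into the interaction at full weight, as they do in a change score. ANCOVA weights baseline by how well it predicts the outcome. The Week 8 estimate is then more precise, from data already collected.
2. **The hypothesis is diffuse.** Two degrees of freedom cover any departure from parallel profiles. A significant result does not say at which visit the arms differ or in which direction. Partial eta squared gives neither, and it does not give a Week 8 difference in L/min or metres.

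At stake are power in a 70-student trial and a primary p-value that is hard to read.

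**Working it through.** **Inputs from the protocol article:** two arms, 1:1; three visits; f = 0.25; alpha 0.05; power 0.80; 28 per group before attrition and 35 after. **Assumed, because the article gives none of them:** correlation ρ between visits, shape of the effect over time, and a Week 8 difference of 0.5 SD. Compound symmetry is used unless stated otherwise.

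**The plan's own figure.** For the interaction, λ = f²·N·3/(1−ρ), with 2 and 2(N−2) degrees of freedom. With ρ = 0.5 and no sphericity correction, N = 28 in total gives λ = 0.0625·28·3/0.5 = 10.5 and power 0.81. N = 56 gives λ = 21 and power 0.99. So 28 per group does not reproduce at those settings; ρ = 0 comes close (54 in total). The attrition step does reproduce: 28/0.8 = 35. The mismatch is a separate matter and is not used below.

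**What f = 0.25 means at Week 8.** Let d be the Week 8 difference in SD units. For arm differences of 0, d/2, d at Weeks 0, 4, 8, the cell effects are ±d/4, 0, ±d/4, so f = d/√24 = 0.2041d. For a plateau (0, d, d) or late effect (0, 0, d), f = d/√18 = 0.2357d. Hence f = 0.25 with a linear build-up is d = 0.25·√24 = 1.22 SD.

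**Interaction, 28 per arm, d = 0.5, linear, ρ = 0.5.** f² = 0.25/24 = 0.01042; λ = 0.01042·56·3/0.5 = 3.5; power 0.36.

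**Week 8 ANCOVA, same setting.** SE = √[(2/28)(1−ρ²)] = √(0.0714·0.75) = 0.231; d/SE = 2.16; t with 53 df; power 0.56.

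| ρ | Interaction, linear | Interaction, late or plateau | Week 8 ANCOVA |
|---|---|---|---|
| 0.5 | 0.36 | 0.46 | 0.56 |
| 0.7 | 0.56 | 0.69 | 0.73 |
| 0.8 | 0.75 | 0.86 | 0.86 |

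Simulation agrees: 0.358 against 0.557 at ρ = 0.5 (linear), and 0.749 against 0.864 at ρ = 0.8. With all 35 per arm, linear, ρ = 0.5, the figures are 0.44 and 0.66.

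**Why ANCOVA gains at Week 8.** Change from baseline has variance 2(1−ρ) and ANCOVA has 1−ρ² = (1−ρ)(1+ρ). The second is smaller for every ρ < 1.

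**Where the gain fails.** With AR(1) correlation 0.8 and 35 per arm, a plateau effect gives 0.81 for the interaction (Greenhouse–Geisser) against 0.76 for ANCOVA; a late effect gives 0.82 against 0.77. At f = 0.25 (d = 1.22, linear, ρ = 0.5, 28 per arm) both tests have at least 0.98.

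**Effect at Week 4 only, none at Week 8** (ρ = 0.5, 28 per arm). A 0.8 SD difference gives f = 0.2357·0.8 = 0.189, λ = 11.9, and a significant interaction in 87% of trials; a 0.5 SD difference gives about 46%. Week 8 ANCOVA rejects in about 5%. If a significant interaction is followed by a Week 8 between-arm t-test at 0.05/3 (an assumed rule, since the article names no method), a Week 8 claim follows in about 1 to 2% of trials.

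**The case against.** A reader might infer that the plan can declare the programme successful when there is no Week 8 effect. The documents do not support that. The article states no success rule beyond the significance threshold. It plans adjusted pairwise comparisons after a significant interaction, and under the assumed Bonferroni rule these lead to a Week 8 claim in only about 1 to 2% of trials with a Week 4 effect alone. Nor is the 87% a false-positive rate: a real Week 4 difference is a real interaction, and under the full null the test rejects in about 5%.

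The power comparison also rests on assumed values, and some favour the interaction. By the trial's own design effect almost nothing is lost, although 1.22 SD is large. A question about trajectories is legitimate, analysis and sample size agree on it, and a statistical analysis plan not at hand may name a time point. The sentence "PEFR values will be interpreted with consideration of participant age, sex, and anthropometric characteristics where appropriate" concerns interpretation; it neither promises nor contradicts covariate adjustment.

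All of this stands, and it limits the point to efficiency and focus. It does not remove it. The article does fix the model, with baseline as a level. The pairwise comparisons run only after a significant interaction, so they inherit its power. They are not described as adjusted for baseline, and no Week 8 between-arm contrast is singled out. Where the interaction beats ANCOVA, it does so by drawing on Week 4, and that rejection is not a conclusion about Week 8.

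**Conclusion.** The point holds as a recommended improvement to a valid analysis. For a 0.5 SD Week 8 effect that builds linearly, under compound symmetry with 28 completers per arm, baseline-adjusted Week 8 ANCOVA adds about 0.20 to power at ρ = 0.5, 0.17 at ρ = 0.7 and 0.12 at ρ = 0.8. For late or plateau effects the gain is about 0.10 at ρ = 0.5 and nil at ρ = 0.8. It can turn into a small loss when correlation falls with time, and it is negligible at f = 0.25. The effect size, shape and correlation are all assumptions. Taking Week 8 as the target is a reading of an eight-week programme with a single post-intervention visit, not something the article states. Apart from power, a significant interaction alone does not establish a Week 8 effect, whichever assumptions are used.

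**What to change.** For each primary outcome, make the primary analysis the between-arm difference at Week 8 adjusted for the baseline value of that outcome, reported in original units with a 95% confidence interval. Either of two forms will do:

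- ANCOVA of the Week 8 value on arm and baseline; or
- the Week 8 contrast from a longitudinal model with baseline means constrained equal between arms, which also uses the Week 4 data, for instance from students who miss Week 8.

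Keep the Week 4 comparison and the group × time test as secondary. Settle this before outcome data are seen.

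The cost is wording: no new data are needed, and SPSS 29 can fit the analysis. There are two drawbacks. With plain ANCOVA, Week 4 does not contribute to the primary test. The Sample size calculation section must also be rewritten for the new test, with a Week 8 difference, an SD and a correlation. That rewrite may be uncomfortable: at 0.5 SD and ρ = 0.5, 80% power needs about 48 completers per arm with ANCOVA. That is fewer than the 78 for the interaction with a linear effect, but more than the 35 planned.

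### Pairwise comparisons and Cohen's d are described only for significant interactions; no signed between-arm difference with an interval is fixed regardless of the p-value

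*Protocol article*

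**What the plan says.** All of the following stands in the protocol article.

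- **Test (Data analysis).** "A mixed-design repeated-measures ANOVA will be used to examine group (intervention vs control) × time (baseline, mid-intervention [Week 4], and post-intervention [Week 8]) interaction". This applies to the primary and the secondary outcomes alike. The threshold is given as "Statistical significance will be set at p < 0.05".
- **Follow-up (Data analysis).** "Significant interaction effects will be explored using post hoc pairwise comparisons with adjustment for multiple comparisons".
- **Measures of effect (Data analysis).** Partial eta squared is reported for the ANOVA, with no condition on the p-value. For the follow-up step, "Cohen’s d will be calculated for post hoc pairwise comparisons".
- **Aim (Data analysis).** The intention-to-treat approach is justified partly because it should give a pragmatic estimate of how effective the programme is.
- **Design values (Sample size calculation).** "a medium effect size (f = 0.25), alpha level of 0.05, and statistical power of 0.80 were used for the sample size calculation", leading to the statement that "a minimum of 28 participants per group was required". This is raised to 35 per group for 20% attrition.

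No between-arm mean difference and no confidence interval is named. Means and standard deviations are mentioned for baseline characteristics.

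**The concern.** The section is not silent on effect reporting. It names the effect measures and the step to which each belongs, and the signed one sits behind a significance test. This has three consequences.

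1. **Non-significant interaction.** What remains is the F test and partial eta squared. Partial eta squared is a ratio of sums of squares, so benefit and harm of equal size give the same value. It is not expressed in L/min, metres or score points, and it mixes baseline, Week 4 and Week 8. A reader cannot use it to tell whether a worthwhile effect was excluded or the trial was too imprecise.
2. **Significant interaction.** An estimate shown only because a test passed is, on average, too large when power is low.
3. **Undefined pairs.** Pairwise comparisons after a 2 × 3 ANOVA may be between arms at a visit or between visits within an arm. Only the first answers the randomised question, and the section does not choose.

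This sits badly with the section's own aim of estimating effectiveness.

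**Working it through.** **Inputs from the protocol article:** 2 arms, 3 visits, alpha 0.05, f = 0.25, 28 per group required, 35 per group enrolled. **Assumed, because the article does not give them:** equal correlation ρ between visits, SD 1 at each visit, sphericity, and a Week 4 effect half the Week 8 effect d.

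**Step 1. The plan's own figure.** Noncentral F for the interaction: λ = f²·N·3/(1 − ρ), with df 2 and 2(N − 2).
- ρ = 0: 80% power needs 54 in total (27 per group). At N = 56, λ = 0.0625 × 56 × 3 = 10.5 and power is 0.82, close to the stated 28 per group.
- ρ = 0.5: 28 in total is enough, and power at N = 56 is 0.99.
- Attrition: 28/0.8 = 35, as stated.

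The article gives no correlation, so its sample size can be neither confirmed nor refuted here. That is a separate matter; the formula is used below only to set power.

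**Step 2. f in terms of the Week 8 effect.** With between-arm differences of 0, d/2 and d, the centred differences are −d/2, 0 and d/2, and each arm carries half of each. The mean square over the six cells is 4 × (d/4)²/6 = d²/24, so f = d/√24. The design's f = 0.25 therefore corresponds to d = 0.25 × 4.90 = 1.22 SD at Week 8.

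**Step 3. Power at a smaller effect.** For d = 0.5, f² = 0.25/24 = 0.0104. With N = 56 and ρ = 0.5, λ = 0.0104 × 168/0.5 = 3.5 on 2 and 108 df, and power is 0.36. So about 64% of such trials would not reach the follow-up step. Power is about 0.50 at d = 0.6 and 0.76 at d = 0.8.

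**Step 4. Exaggeration after selection.** In 20,000 simulated trials per setting, the estimate was kept only if the interaction p was below 0.05. The factor is the mean kept estimate divided by the true effect.

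| Per arm | ρ | True d at Week 8 | Power | Factor, Week 8 difference | Factor, difference in change |
|---|---|---|---|---|---|
| 28 | 0.5 | 0.5 SD | 36% | 1.25 | 1.5 |
| 35 | 0.5 | 0.5 SD | 44% | 1.2 | 1.4 |
| 28 | 0.8 | 0.5 SD | 75% | 1.07 | 1.14 |
| 28 | 0.5 | 0.8 SD | 76% | 1.07 | 1.13 |
| 28 | 0 | 1.22 SD (f = 0.25) | 82% | 1.05 | 1.10 |
| 28 | 0.5 | 1.22 SD (f = 0.25) | 99% | 1.00 | 1.01 |

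**Step 5. Partial eta squared has no direction.** With 28 per arm and ρ = 0.5, its mean was 0.048 for a true effect of +0.5 SD and 0.048 for −0.5 SD.

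**Step 6. What an unconditional estimate would offer.** The approximate 95% half-width for the Week 8 difference is 1.96·√(2/n): 0.52 SD at 28 per arm and 0.47 SD at 35. Baseline adjustment multiplies it by √(1 − ρ²). With ρ = 0.5 this gives 0.52 × 0.866 = 0.45 SD at 28 per arm and 0.41 SD at 35.

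**The case against.** An omnibus interaction test followed by adjusted comparisons is a conventional and internally consistent ANOVA procedure, and a condensed article may leave reporting of means and intervals to a fuller document. This limits what can be claimed. Several stronger readings are tempting but are not supported.

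- **That comparisons are made solely after significance.** The section describes them for significant interactions but does not exclude others. An analysis plan not shown could add unconditional differences. The point is about the procedure as written.
- **That a non-significant trial gives no effect estimate.** Partial eta squared is still reported. What is not provided for is a signed between-arm estimate with an interval.
- **That any significant result is materially inflated.** This depends on power. At the design's f = 0.25 the inflation is about 0 to 10%. The 0.5 SD effect and the correlations are assumptions, and the 1.5-fold figure applies to the difference in change, a contrast the section does not name.
- **That non-significance is likely for any effect below 1 SD.** With 28 per arm and ρ = 0.5 it is the likelier result only below about 0.6 SD.
- **That within-arm inference is planned.** Outcome measures says that "changes in PEFR will be interpreted alongside baseline performance and repeated assessment trends", but this concerns clinical interpretation where no minimal important difference is established. The inferential test is group × time, which compares the arms.

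What survives is that the article does state a rule, and that rule ties the only signed measure to significance and leaves the pairs undefined.

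**Conclusion.** The point holds in this limited form. As written, Data analysis provides a signed effect measure only for significant interactions, does not define the pairs, and otherwise offers an unsigned, unitless summary over three visits. The loss in the non-significant branch needs no assumption about effect size: without a signed difference and an interval, no effect and too little precision look alike. The bias in the significant branch is conditional on power. Under compound symmetry and a linear effect of 0.5 SD at Week 8, the Week 8 difference is exaggerated by about 7% (28 per arm, correlation 0.8) to 25% (28 per arm, correlation 0.5), and it is close to negligible if the true effect is as large as the design assumes. It should be changed, but it does not invalidate the trial.

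**What to change.** In Data analysis, state that for each primary and secondary outcome the baseline-adjusted between-arm difference at Week 8, and at Week 4, will be reported with its 95% CI in natural units (L/min, metres, score points), whatever the interaction p-value. State also that the conclusion rests on the Week 8 between-arm estimate and its interval, not on within-arm changes or partial eta squared. If post hoc comparisons are kept, say that they are between arms at each visit.

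Cost: a short text change and one added model per outcome, either an ANCOVA or a longitudinal model with baseline as covariate. The stated ANOVA cannot supply these estimates because it treats baseline as a level of time. No extra participants, visits or data are needed.
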